### Statistical analysis

The primary analysis will compare length of stay in hospital at readmission after the index hospital admission during 12 months of follow up between intervention and control conditions, using generalised linear mixed models with a negative binomial distribution, accounting for clustering by wards and adjusting for credible confounders to further control baseline imbalance. The approach will be intention to treat.

Secondary analyses will compare time to event of readmission between intervention and control conditions using survival analysis, and frailty status, quality of life outcomes and readmission rates using linear mixed models, accounting for clustering by ward and adjusting for credible confounders.

Covariables to be considered in these analyses will include age, sex, degree of frailty at index admission, number of hospitalisations in the preceding 12 months, cognition (MMSE score), and primary admission diagnosis for the index admission and for readmissions. SAS and R statistical software will be used for analysis.

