## Methods

### Design

The FORTRESS trial is a multi-site hybrid type II stepped wedge, cluster randomised trial to be conducted over three years (see Fig. 1). This study protocol is reported in accordance to the Standard Protocol Items: Recommendations for Intervention Trials (SPIRIT) checklist available as supplementary file. The hybrid type II trial approach [20] allows testing of the implementation strategy (Implementation Facilitation [21]) and testing the outcomes of the intervention (screening for frailty and use of appropriate interventions).

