**Fig. 1 Fig1:**
[figure not shown]
Overview of the FORTRESS stepped wedge design Participants and sites. SALHN – Southern Adelaide Local Health Network, South Australia. HKH – Hornsby Ku-ring-gai Hospital, New South Wales

The FORTRESS trial builds on previous research conducted by members of the research team. Cameron et al., [22] evaluated the efficacy of a multicomponent interdisciplinary intervention with community dwelling older people after completion of their contact with health services in the Frailty Intervention Trial (FIT). Interventions included multiple sessions of physiotherapy and dietetics, with limited comprehensive geriatric assessment over a period of 12 months. Results of FIT included reduced frailty, improved physical performance, and increased degree of independence for community dwelling older people [22, 23]. Economic evaluation revealed that in very frail older people residing in the community, the multicomponent interdisciplinary intervention was both more effective and less costly than usual care [23, 24].

The protocol for this study has been approved by the Northern Sydney Local Health District Human Research Ethics Committees and is registered at www.ANZCTR.org.au (ACTRN12620000760976p).

The FORTRESS trial will be conducted across six inpatient wards at two different states (Hornsby Ku-ring-gai Hospital, Northern Sydney Local Health District in New South Wales, and Southern Adelaide Local Health Network in South Australia). Older people will be included if they are aged 75 years or older; admitted to the six wards included within the participating local health districts; assessed as frail (score of 3 or above out of 5 on the FRAIL scale [8]); living at home in the community; and score 24 or above out of 30 on the Mini Mental State Exam [25]. People will be excluded if they are admitted to hospital with a new diagnosis of stroke (people with acute stroke are admitted to specialised units in both participating hospitals), have an illness likely to be associated with a life expectancy of < 12 months (assessed on the modified version Illness Severity Rating [20]); are unable to cooperate with the intervention program; were not mobile prior to admission; or reside in a residential aged care home. 

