### Sample size

The projected enrolment is approximately 732 participants from the six wards over 16 months. This sample size enables detection of a mean difference of 35 days versus 50 days in total length of hospital stay at readmission after the index admission during 12 months of follow up, with 80% power at significance level 5%, allowing for 10% mortality, 10% dropout, and a design effect of 1.75 for clustering by wards.

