### Randomisation procedure

Transition to the intervention phase will be randomised by ward with stratification by site and using minimisation with a random component to optimise baseline and sequential balance. To do this the minimisation algorithm will use anticipated ward characteristics including the type of ward, typical length of stay, high or low tendency to discharge to a day rehabilitation ward rather than home and, where possible, typical readmission rates at that ward.

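### The stated stepped-wedge models name no term for calendar period or step, so part of any secular trend would load on the intervention effect

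*Protocol article*

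**What the plan says.** The Design section sets the framework: "The FORTRESS trial is a multi-site hybrid type II stepped wedge, cluster randomised trial to be conducted over three years". There are six clusters: "The FORTRESS trial will be conducted across six inpatient wards at two different states". The order in which they cross over is randomised: "Transition to the intervention phase will be randomised by ward with stratification by site and using minimisation with a random component". The Intervention section makes treatment depend on whether the ward is in its control or its intervention phase at the time of admission.

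The Statistical analysis section gives the primary model for readmission days as a comparison "using generalised linear mixed models with a negative binomial distribution, accounting for clustering by wards and adjusting for credible confounders". It adds that the purpose of the adjustment is to deal further with imbalance at baseline. The secondary models (survival analysis for time to readmission; linear mixed models for frailty, quality of life and readmission rates) repeat the ward clustering and confounder adjustment. The candidate covariables follow: "Covariables to be considered in these analyses will include age, sex, degree of frailty at index admission", then prior hospitalisations, MMSE score and admission diagnosis. All are patient-level. No section mentions period, step, calendar time or secular trend in connection with any model.

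The Sample size section gives the scale: "The projected enrolment is approximately 732 participants from the six wards over 16 months", to detect a "mean difference of 35 days versus 50 days in total length of hospital stay at readmission", with 80% power at 5%, 10% mortality, 10% dropout and a design effect of 1.75 attributed to ward clustering.

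**The concern.** In a stepped wedge, phase and calendar time are confounded by construction, because each ward's control patients are admitted before its intervention patients. Randomising the order of crossover lets the two be separated, since at a given date some wards have crossed and others have not. The analysis uses that information properly only if it conditions on time. A ward effect alone removes differences between wards and leaves mainly a before-after contrast within each ward. The minimisation in the Randomisation procedure section balances ward characteristics over the order of transition, but it cannot change the fact that control comes first.

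At stake is the validity of the primary estimate. If readmission days drift over recruitment for reasons unrelated to the intervention (service changes, bed pressure, admission practice), part of that drift would be reported as effect. A fall would flatter the intervention and a rise would hide a benefit. The same applies to every secondary outcome.

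**Working it through.** **Inputs from the protocol article.** Six wards; 732 participants; 16 months of recruitment; 35 v 50 days (ratio 0.70); 80% power; 5% level, taken as two-sided; 10% mortality; 10% dropout; design effect 1.75.

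**Assumptions.** Equal periods, all wards control in the first and intervention in the last; 2, 3 or 6 steps; 732 × 0.9 × 0.9 = 593 analysed; random ward intercept; linear trend on the log scale.

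**1. The plan's own figure.** No SD or dispersion is stated, so 732 cannot be reproduced independently, only solved backwards. Effective total = 732 × 0.81 / 1.75 = 338.8, or 169.4 per arm. From n = 2 × SD² × (1.96 + 0.84)² / 15², SD = 49.3 days. With 0.80 in place of 0.81, SD = 49.0. So 732 is consistent with an SD of about 49. The trend results in steps 3 and 4 do not use this SD.

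**2. ICC implied by 1.75.** Reading it as 1 + (m − 1) × ICC: with m = 732/6 = 122, ICC = 0.75/121 = 0.0062; with m = 593/6 = 98.8, ICC = 0.75/97.8 = 0.0077.

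**3. How much trend reaches the treatment effect.** Within any ward, intervention patients enter on average 8 months after controls (half of 16). Pooled over wards the gap is smaller. With 3 steps (4 periods of 4 months), the mean control period is 4/6 = 0.67 and the mean intervention period 14/6 = 2.33; the gap is 1.67 × 4 = 6.7 months. With 6 steps: 35/21 = 1.67 and 91/21 = 4.33; the gap is 2.67 × 16/7 = 6.1 months. A random-ward model weights the two contrasts. Generalised least squares on ward-period means gives:

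| Steps | Months of trend absorbed, no period term (ICC 0.006–0.05) | With period terms | Design effect with period terms (ICC 0.006–0.008) |
|---|---|---|---|
| 6 | 6.7–7.6 | 0 | 2.1–2.2 |
| 3 | 7.1–7.8 | 0 | 2.6–2.7 |
| 2 | 7.4–7.8 | 0 | 3.4–3.5 |

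**4. Illustration with no true effect.** Spurious ratio = (1 − annual decline)^(months/12).

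- 10% per year: 0.90^(6.7/12) = 0.94 to 0.90^(7.8/12) = 0.93.
- 20% per year: 0.80^(6.7/12) = 0.88 to 0.80^(7.8/12) = 0.86.
- A rise of 20% per year gives 1.11 to 1.13, so a true 0.70 would appear as about 0.78.

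The SE implied by the design is ln(50/35)/2.80 = 0.357/2.80 = 0.127. Type I error is Φ(−1.96 + |b|/0.127) + Φ(−1.96 − |b|/0.127), where b is the log of the spurious ratio. It is about 7–8% for a 10% yearly decline and 16–21% for 20%.

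A negative binomial simulation (dispersion 1.35, fixed ward effects standing in for the mixed model, 600 replicates, 3 and 6 steps) used a fall of 20% between the first and last period. It rejected in 23–29% of runs without period terms and in about 6% with them. With no drift, the model without period terms rejected in 3.5–4.8% of runs.

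**5. Power with time in the model.** Power = Φ(15/SE − 1.96), SE = SD × √(4 × DE/593), SD 49.2. For 6 steps and DE 2.14, SE = 5.91 and power is 72%. Over the ICC range it is about 71–72% (6 steps), 62–63% (3 steps) or 51–52% (2 steps), against the stated 80%.

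**The case against.** The best defence is that the model is left open. The covariables are candidates to be considered, the adjustment is for plausible confounders, and time is the obvious confounder in a design the article itself calls stepped wedge. A journal article condenses, and a SAP not seen here may contain the term. This stands to the extent that a time term is not excluded, and a reader who inferred that the investigators have decided against one would go beyond the document. It does not dispose of the point. The article does not defer the model: it gives the distribution, the clustering term, the purpose of adjustment and the covariables, and leaves out the term that identifies the effect in this design. Open wording would also allow its inclusion to be decided after the data are seen.

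Four further inferences are tempting and not supported.

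- That all of any drift is counted as effect. About 7–8 of the 16 months' worth is.
- That the type I error is wrong whatever happens. It is inflated only if a trend exists, and the document gives no evidence of one or of its size.
- That seasonality biases the primary outcome. Each complete follow-up spans 12 months, so annual seasonality largely averages out. Some could remain through case mix at entry, incomplete follow-up or readmissions soon after discharge.
- That leaving out site is a comparable defect. Wards are nested within sites, so the ward effect already carries much of any site difference. A fixed site effect is a modelling preference.

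**Conclusion.** The point holds in this form: the primary and secondary stepped-wedge models, as stated, name no term for calendar period or step and would give a time-confounded estimate if fitted that way. Under the assumed layouts, about 7–8 months' worth of any linear trend loads on the intervention effect, in either direction. Conditioning on period removes it entirely when the trend is common to all wards. The ratio of 0.86–0.88 for a 20% per year decline is an illustration, not an estimate of actual bias.

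The power consequence is real but conditional. The design effect of 1.75 is attributed to ward clustering only, and how it was derived is not stated. The figures of 2.1–3.5 rest on reading it as a conventional clustering inflation and on the number of steps. They show that 80% should be rechecked, not that a particular shortfall is established. Because the validity of the primary comparison depends on the time term, it should be settled before analysis.

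**What to change.** State in the protocol and SAP that the primary negative binomial mixed model contains intervention phase, fixed effects for calendar period (step) of index admission, and the ward effect, and that every secondary model carries the same period terms. Site-by-period effects can be an optional sensitivity analysis. With six wards a more parsimonious function of time could also be defended, provided it is fixed in advance.

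No new data should be needed, because the date of index admission is required anyway to define the 12 months of follow-up. The cost is a wider confidence interval and probably less power than stated. The sample size statement should therefore be recalculated with the actual number of steps, a stated SD or dispersion, a stated ICC and time in the model, and the resulting power reported in place of 80% if it differs.

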#### Secondary outcomes

Frailty status at baseline, 3 months and 12 months measured using the FRAIL Scale [8].Quality of life at baseline, 3 months and 12 months measured using the EQ-5D-5L [27].Time-to-event of readmission, and readmission rates at 3 months and 12 months.

Baseline measures are assessed by the study Implementation Clinician on the ward at admission. Follow-up outcome assessment will take place via telephone at 3 and 12 months by a health professional masked to group allocation. Each assessment will include administration of the FRAIL Scale to measure frailty and EQ-5D-5L to measure quality of life. Data regarding overnight non-elective hospital readmissions will be obtained from participant self-report, and from public hospital electronic medical records for hospital readmissions.

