### Economic analysis

The total cost of delivering the intervention will be assessed, and cost-effectiveness analyses will be conducted, according to the principles for conducting economic evaluation alongside stepped wedge trials [30]. The economic evaluation will take the perspective of the health care funder and will include analyses for health outcomes measured in terms of the main clinical outcomes, including cost per extra person avoiding readmission, cost per extra person avoiding frailty, and cost per quality adjusted life years (QALY) gained based on the EQ-5D-5L. The study will collect data on the cost to deliver the intervention (including staff costs, training, capital costs and consumables), and inpatient hospital admissions, based on DRG-related costs. Using the mean costs in each trial arm, and the mean health outcomes in each arm, the incremental cost per extra person avoiding frailty, per extra person avoiding re-admission and per QALY gained of the intervention group compared with control group will be calculated; results will be plotted on a cost-effectiveness plane. Bootstrapping will be used to estimate a distribution around costs and health outcomes, and to calculate the confidence intervals around the incremental cost-effectiveness ratios. One-way sensitivity analysis will be conducted around key variables. A probabilistic sensitivity analysis will be conducted to estimate the joint uncertainty in all parameters, and a cost-effectiveness acceptability curve (CEAC) will be plotted.

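### Readmission rates, a secondary outcome, are assigned to a linear mixed model although they rest on skewed counts with varying follow-up and readmission days in the same section get a negative binomial model

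*Protocol article*

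**What the plan says.** The protocol's Secondary outcomes section lists "Time-to-event of readmission, and readmission rates at 3 months and 12 months" and "Frailty status at baseline, 3 months and 12 months measured using the FRAIL Scale". The Statistical analysis section analyses "frailty status, quality of life outcomes and readmission rates using linear mixed models". Just before that, the same section plans the primary outcome, readmission days, "using generalised linear mixed models with a negative binomial distribution, accounting for clustering by wards".

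The article gives no denominator for the readmission rate, and does not say whether it is a count per person-time or the proportion readmitted. Eligibility defines frailty by a cut-off: "assessed as frail (score of 3 or above out of 5 on the FRAIL scale". The Economic analysis section uses frailty as a yes/no state, in "cost per extra person avoiding frailty".

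**The concern.** Readmission days and readmission counts come from the same records on the same people. One receives a count model and the other a Gaussian model, with no reason given. The section names both model classes, so *linear* is unlikely to be shorthand for *generalised linear*. This makes it a stated choice, not a detail left to the analysis plan.

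A count per person is skewed with a mass at zero, and its variance rises with its mean. A proportion readmitted is binary at the level of the person. A linear model is not the natural choice under either reading. It has no built-in way to handle unequal time at risk, so the result depends on how the rate is constructed beforehand. At stake are the precision of a clinically important secondary result and, if deaths differ between conditions, a modest bias.

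**Working it through.** **Inputs from the protocol.** About 25% of older people readmitted within three months (Discussion, a background figure); 10% mortality, 10% dropout and 732 participants (Sample size); 12 months of follow-up. The 732 was derived for the primary outcome and does not change.

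**Assumed.** Dispersion k between 0.5 and 3, rate ratios of 0.70 to 0.80, and mortality differences between conditions. The protocol states none of these for readmission counts.

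**Share with no readmission.**
- Three months: 1 − 0.25 = 0.75.
- Twelve months, Poisson with constant hazard: 0.75^4 = 0.32.
- Twelve months, negative binomial: three-month mean m = (0.75^(−k) − 1)/k, zero share (1 + 4km)^(−1/k). This gives 0.38 (k = 0.5), 0.43 (k = 1), 0.49 (k = 2) and 0.54 (k = 3).

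A large mass at zero is therefore well supported at three months. At 12 months it is 32 to 54%, depending on the assumption.

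**Bias of raw counts, in closed form.** With exponential death and dropout, mean follow-up in years is (1 − S)/(−ln S), where S = (1 − mortality) × 0.90.
- Mortality 15%: S = 0.765, mean 0.877. Mortality 5%: S = 0.855, mean 0.926. Ratio 0.926/0.877 = 1.055.
- Mortality 20%: S = 0.72, mean 0.852. Mortality 10%: S = 0.81, mean 0.902. Ratio 0.902/0.852 = 1.058.
- Equal mortality: ratio 1, no bias.

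**Simulation.** 366 per condition (732/2), 12 months, 10% dropout, gamma-Poisson counts with k = 1, 600 trials per row. There is no ward clustering and there are no stepped-wedge periods. The negative binomial model was given the true dispersion, which favours it slightly. Each cell shows the median estimated ratio and the share of trials rejecting at 5%.

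| True ratio; mortality control / intervention | Linear, raw count | Linear, count ÷ time | Negative binomial with offset |
|---|---|---|---|
| 1; 10% / 10% | 0.999; 2.7% | 0.999; 3.3% | 0.999; 2.5% |
| 1; 15% / 5% | 1.058; 5.8% | 1.002; 4.3% | 0.998; 5.5% |
| 1; 20% / 10% | 1.063; 9.2% | 1.006; 4.7% | 1.005; 5.2% |
| 0.70; 10% / 10% | 0.703; 91.0% | 0.700; 85.2% | 0.704; 91.8% |
| 0.70; 15% / 5% | 0.736; 81.5% | 0.697; 86.8% | 0.698; 93.2% |

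The linear model on individual rates loses 91.8 − 85.2 = 6.6 and 93.2 − 86.8 = 6.4 points.

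**Sensitivity.** I repeated the comparison with 1,500 trials per setting. At ratio 0.70 the loss was about 6 points for k = 0.5 and k = 1, 4.5 to 4.8 for k = 2, and 3.1 to 4.2 for k = 3. At ratios 0.75 and 0.80 with equal mortality it was 12 points for k = 0.5, 5.4 to 6.6 for k = 1, and 3.9 to 4.8 for k = 2. A loss of about 4 to 10 points covers most settings; the extremes were 3 and 12. Raw counts with equal mortality lost only about 1 to 4 points.

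**The case against.** The strongest defence is that a linear model is serviceable here. A rate difference is a legitimate target, and a secondary outcome need not share the primary outcome's scale. The simulations show no bias and no inflated error when mortality is equal, and the protocol gives only one mortality figure. The zero share borrows a general background figure, and time to readmission is separately covered by survival analysis. All of this stands. It limits the point to efficiency, plus bias under an assumed mortality difference.

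Several stronger readings are tempting, and the document does not support them.
- *The estimates ignore time at risk.* The text says rates, which may already be per person-time. The fair statement is that no denominator is given and a linear model does not supply one.
- *Shortened follow-up of late entrants, mostly under intervention, would mimic a large benefit.* This needs enrolment to run for the full three years. The Sample size section gives 16 months. From December 2020, 16 + 12 = 28 months ends about April 2023, before the December 2023 close.
- *The model does not fit, or misstates intervals in every stepped-wedge period.* The step layout is in a figure not available here, and the simulations do not model periods.
- *A linear model is wrong for frailty.* A mean difference on the 0-5 FRAIL score is common and defensible. Using a score clinically and a threshold in the economic analysis is not a contradiction.

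**Conclusion.** The point holds in a limited form. Assigning readmission rates to a linear mixed model is a stated choice, out of line with the model for readmission days in the same section, and a better one is available at almost no cost. The loss is about 4 to 10 points of power if individual rates are modelled. If raw counts are modelled, the relative bias is about 5 to 7%, and only when mortality differs between conditions by about 10 points.

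These sizes rest on assumed dispersion, effect and mortality differences in a parallel-arm, unclustered setting. They indicate the relative merit of the models and are not the trial's actual power. For frailty, the only requirement is that the model match whichever form, score or status, is analysed. The primary analysis and the sample size are untouched.

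**What to change.** In the Statistical analysis section or the analysis plan, replace the linear model for readmission rates with the following:
- Number of non-elective readmissions at 3 and at 12 months: the same negative binomial mixed model family as the primary outcome, with log time at risk as an offset.
- If the rate means the proportion readmitted: a logistic mixed model. State which meaning applies.
- FRAIL score (0-5) and EQ-5D-5L: the linear mixed model may stay. If frailty is analysed as frail/not frail, as in the economic analysis, use a logistic mixed model.

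The cost is a sentence or two of wording. The count model uses the same family as the primary analysis, and time at risk follows from dates of discharge, death and last contact. The effect becomes a ratio instead of a difference, and with six wards the mixed models may need some convergence work.

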#### Additional measures

Participants will be asked to self-report their weight and current medications at 3- and 12-month outcome assessments. Current medications will be cross-checked through participant’s pharmacists and Home Medicine Review report where available. Covariables to be considered will include age, sex, degree of frailty at index admission, number of hospitalisations in the preceding 12 months, cognition (MMSE score), and primary admission diagnosis for the index admission and for readmissions.

The hybrid nature of this trial allows understanding of both effectiveness and implementation. Figure 2 describes the conceptual model of evaluation [28]. A process evaluation will be conducted concurrently to describe the adaptation, scale and spread of FORTRESS intervention and details will be described in a separate paper. Details are available through the trial registry.

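### Baseline EQ-5D-5L is collected but is not named for adjustment in the quality-of-life model or in the QALY difference

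*Protocol article*

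**What the plan says.** The Secondary outcomes section of the protocol article lists "Quality of life at baseline, 3 months and 12 months measured using the EQ-5D-5L". On who collects the first value, it says "Baseline measures are assessed by the study Implementation Clinician on the ward at admission".

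The Statistical analysis section will compare "frailty status, quality of life outcomes and readmission rates using linear mixed models, accounting for clustering by ward and adjusting for credible confounders". The next paragraph names the variables: "Covariables to be considered in these analyses will include age, sex, degree of frailty at index admission", followed by "number of hospitalisations in the preceding 12 months, cognition (MMSE score), and primary admission diagnosis for the index admission and for readmissions". The Additional measures section gives the same list, opening "Covariables to be considered will include age, sex, degree of frailty at index admission". Baseline EQ-5D-5L is in neither place.

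For the primary analysis, the Statistical analysis section gives the purpose of adjustment: "adjusting for credible confounders to further control baseline imbalance".

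The Economic analysis section includes "cost per quality adjusted life years (QALY) gained based on the EQ-5D-5L". It describes the incremental ratios as calculated from mean costs and mean outcomes in each arm, with bootstrapped uncertainty. It does not mention adjustment for baseline utility.

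**The concern.** A follow-up quality-of-life score is usually predicted best by the same person's earlier score. Leaving that score out has two costs: the interval is wider than the collected data allow, and a baseline difference between conditions carries into the follow-up comparison.

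A baseline difference is plausible in this design:

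- Only six wards are randomised, and a patient's condition depends on the ward's phase at admission, so condition is tied to calendar time.
- Screening, opt-out and baseline assessment all happen once the ward's phase is set. Masking is described for the follow-up assessors only.
- The minimisation factors in the Randomisation procedure section are ward characteristics. None is patient quality of life.

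Baseline frailty is a limited stand-in. Eligibility requires a FRAIL score of at least 3 out of 5, so in this sample it can only be 3, 4 or 5.

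At stake are one secondary outcome and the cost per QALY.

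**Working it through.** **The plan's own figures.** The article gives no SD, correlation, target difference or power for EQ-5D-5L, so there is nothing to reproduce for this outcome. The 732 in the Sample size section concerns readmission days and does not bear on the point.

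**1. Precision in the quality-of-life model.** Let r be the correlation between baseline and follow-up EQ-5D-5L, a the correlation of baseline frailty with baseline EQ-5D-5L, and b the correlation of baseline frailty with follow-up EQ-5D-5L. All three are assumed. If frailty is already in the model, the further proportional cut in residual variance from adding baseline EQ-5D-5L is p², with

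p = (r − ab) / √[(1 − a²)(1 − b²)].

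| r | a | b | p | variance cut p² |
|---|---|---|---|---|
| 0.4 | 0.5 | 0.4 | 0.20/√(0.75 × 0.84) = 0.252 | 6.3% |
| 0.5 | 0.4 | 0.3 | 0.38/√(0.84 × 0.91) = 0.435 | 18.9% |
| 0.6 | 0.3 | 0.3 | 0.51/0.91 = 0.560 | 31.4% |

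The first and last rows are the extremes over r = 0.4 to 0.6, a = 0.3 to 0.5 and b = 0.3 to 0.4. The standard error is multiplied by √(1 − p²), which is √0.937 = 0.968 to √0.686 = 0.828, so it is about 3% to 17% smaller. A comparison with 80% power without the baseline value (two-sided 5%) would have power Φ(2.80/√(1 − p²) − 1.96), which is 82.5% to 92.3%.

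With no other covariate in the model, the cut is r². That is 9%, 25% or 49% for r = 0.3, 0.5 or 0.7, which is too generous here because frailty and other variables are listed.

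**2. Carry-over in the quality-of-life model.** Take an assumed baseline gap of 0.05 utility between conditions and a baseline to follow-up slope equal to the correlation (equal variances). The amount carried into the follow-up difference is 0.05 × slope: 0.015, 0.025 or 0.035 for slopes of 0.3, 0.5 and 0.7. The listed covariates would remove part of this, by an amount the document does not let us calculate.

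**3. Carry-over in the QALY difference.** The article does not give the QALY formula. Assume area under the curve with straight lines between 0, 3 and 12 months, and complete data in survivors:

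QALY = 0.25(u0 + u3)/2 + 0.75(u3 + u12)/2 = 0.125·u0 + 0.5·u3 + 0.375·u12.

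With the same gap and the same slope at both follow-ups, the spurious difference is 0.05 × (0.125 + 0.875 × slope):

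- slope 0.3: 0.05 × 0.3875 = 0.019 QALY
- slope 0.5: 0.05 × 0.5625 = 0.028 QALY
- slope 0.7: 0.05 × 0.7375 = 0.037 QALY

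The baseline value is itself part of the area. A gap would therefore enter the QALY difference even with a slope of zero (0.05 × 0.125 = 0.006).

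**The case against.** The strongest reply is that this is a condensed article and that the exact model for a secondary outcome belongs in an analysis plan. The wording is open: the variables are to be considered, the list includes rather than exhausts, and a baseline score could count as a credible confounder. One list serves the readmission, survival and mixed models together, so an outcome-specific baseline would not sit naturally in it, and frailty may be there simply as a general prognostic factor. A linear mixed model on data from 0, 3 and 12 months may already take baseline as a response. The listed variables also correct part of any imbalance. The economic evaluation is described separately and follows cited principles for stepped wedge trials that are not shown.

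Much of this stands. A reader might infer that the plan certainly gives away precision and leaves imbalance in quality of life uncorrected. The document does not support that: nothing excludes baseline EQ-5D-5L, and the listed covariates give some indirect correction. Nor does it support reading the 9% to 49% variance cut as a saving in participants. Those figures rest on assumed correlations, ignore covariates already listed, and apply to individual-level residual variance. They do not convert directly in a six-ward trial with a stated design effect of 1.75.

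The reply does not remove the point. The list is written out twice, is applied to these outcomes, and omits the variable that most directly serves the stated purpose of controlling baseline imbalance. Having a mixed model is not enough either. If baseline is a response with means left free in each condition, the follow-up contrast is in essence unadjusted; the gain comes from constraining the baseline means to be equal. Openness in the list also allows the choice to be made after any imbalance has been seen.

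**Conclusion.** The concern holds in a limited form. As written, the named covariates include baseline frailty but not baseline EQ-5D-5L, and cost per QALY is described from arm means without adjustment for baseline utility. If that is what is done, imbalance in quality of life is corrected only indirectly in the quality-of-life model and not at all in the QALY difference, and precision is lost.

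The size depends on correlations that the document does not give. On the assumptions above, the further residual variance cut is about 6% to 31% with frailty already adjusted for, before allowing for the other listed covariates and for clustering. A 0.05 utility gap, also assumed, would move the QALY difference by about 0.02 to 0.04. Because baseline is taken during an acute admission, the correlation with later scores could be at or below the low end of the range. The primary outcome and the sample size of 732 are unaffected.

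**What to change.** In the Statistical analysis section, state that the quality-of-life linear mixed model at 3 and 12 months includes baseline EQ-5D-5L utility as a covariate. Alternatively, state that baseline is modelled as a response with means constrained equal across conditions; this is about as efficient. Make the same addition to the list in the Additional measures section.

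In the Economic analysis section, state that the QALY difference is estimated with adjustment for baseline utility, for example by regression within each bootstrap sample, rather than as a difference in raw arm means.

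If an analysis plan already says this, a cross-reference is enough. The cost is a phrase in each section, settled before the data are analysed. No extra data collection is needed and the sample size does not change.
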